#### 2.8.2 Secondary outcomes

(1) Sleep quality: Pittsburgh Sleepiness Index (PSQI) and sleep duration. The PSQI scale is used to assess the sleep quality of the patient in the past month. It consists of 5 other-rated items and 19 self-rated items. All other-rated items and the 19th self-rated item are not scored. The 18 items involved in the scoring are divided into 7 parts: sleep quality, sleep onset, actual sleep time, sleep efficiency, sleep interference, drug-assisted sleep, and daytime energy. Each part is scored 0–3 points according to the level, and the scores of each item are added up to the total score of the PSQI scale. The score range is 0–21 points. The higher the score, the more severe the insomnia; conversely, the lower the score, the better the sleep quality.

(2) The quality of life: Questionnaire on the impact of nocturia on quality of life (N-QOL scale score). The N-QOL scale is used to assess the quality of life of the test subject in the past 2 weeks. It is divided into 3 dimensions and 13 questions, including 7 questions on energy/sleep (0–28 points), 5 questions on distress/concern (0–20 points), and 1 question on self-assessment of quality of life (0–4 points). Each question is scored 0–4 points. Questions 12 and 13 are reverse-scored questions with a score range of 0–52 points. The lower the score, the lower the quality of life, and vice versa.

(3) Therapeutic efficacy of traditional Chinese medicine syndromes: TCM syndrome scoring scale. Record the patient’s TCM symptoms, including tongue and pulse, nocturia, dry mouth and drinking water, etc. The higher the score, the more serious the patient’s condition.

(4) The level of AVP and ANP.

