**FIGURE 1 F1:**
[figure not shown]
The flow chart of the clinical procedures.

**TABLE 1 T1:** Schedule of enrollment, intervention and assessment.

Time point	Enrollment Week -1	Allocation Week 0	Treatment phase Week 1-2	Follow-up Week 3	Follow-up Week 10

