One treatment cycle consists of 5 days of treatment followed by 2 days of rest, with 2 consecutive treatment cycles being administered. To isolate the effects of the experimental intervention, all enrolled participants (both intervention and control groups) will be instructed to refrain from receiving any additional moxibustion treatments or traditional Chinese medicine therapies (e.g., acupuncture, cupping, herbal medicine) during the 8-week study period. These restrictions were communicated verbally and in written form at enrollment. And participants will be requested to complete weekly diaries to report any inadvertent use of prohibited therapies.

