### 2.7 Procedure

Prior to the commencement of therapy, the practitioner ought to document the patient’s nocturia frequency, administer and record the Pittsburgh Sleep Quality Index (PSQI) and Nocturia Quality of Life (N-QOL) scale scores, assess the traditional Chinese medicine syndrome score, and evaluate the intensity of nocturia and urinary frequency. Upon the morning subsequent to enrollment, fasting blood samples will be procured for the assessment of AVP and ANP levels. Throughout the treatment period, nocturia frequency will be meticulously recorded on a daily basis.

Upon completion of the treatment regimen, the PSQI, N-QOL scale scores, and traditional Chinese medicine syndrome score will be reassessed, and fasting blood samples will be collected the subsequent morning for a repeat analysis of AVP and ANP. Additionally, 2 months post-treatment, these assessments–including the PSQI, N-QOL scale scores, traditional Chinese medicine syndrome score, and fasting blood tests for AVP and ANP–will be conducted once more.

Ultimately, a comprehensive evaluation will encompass the nocturia frequency, sleep quality, quality of life, traditional Chinese medicine syndrome scores, as well as AVP and ANP levels, for both patient cohorts, both pre- and post-treatment, with a further assessment conducted 2 months after the conclusion of therapy. Figure 1 illustrates the clinical procedures during the research.

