### 2.9 Sample size

Based on relevant research (significance level, take α = 0.05, β = 0.10, test power 1-β = 0.90; two-sided test, confidence level 95%, *Z* = 1.96, *E* = 10%, *P* = 0.5), the estimated sample size is 96 cases preliminary. If the dropout rate is considered to be at most 15%, the total number of cases in the two groups should be at least 110. Therefore, 55 participants were recruited in each group.

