### 2.12 Data collection and analysis

The data of various observation indicators of patients were collected on the day of treatment, the day after the end of treatment and 2 months after the end of treatment. To ensure the accuracy and completeness of the data, we will adopt a double-entry method. PASW Statistics 18.0 software was used to establish a database for case investigation data that met the inclusion criteria, and data review was performed after data entry was completed.

The statistical analysis of the PASW Statistics 18.0 data was performed, encompassing descriptive statistics for clinical baseline data. For continuous outcomes, group differences will be analyzed using Student’s *t*-tests if data are normally distributed; otherwise, the Mann-Whitney U test will be applied. For categorical variables, Chi-square tests or Fisher’s exact tests will be used as appropriate. Efficacy evaluations utilized both intention-to-treat (ITT) and per-protocol (PP) populations, while safety assessments were conducted on the safety analysis set. In the intention-to-treat analysis, missing data due to withdrawal or dropout will be handled using the last observation carried forward (LOCF) method. Participants who received prohibited therapies were retained in the trial per the ITT principle but flagged for sensitivity analysis. Their data were analyzed both within the full cohort and in a subgroup excluding protocol violators. When necessary, multiple imputation methods will be considered for missing value replacement, or alternative approaches will be selected based on actual circumstances. For clustering, the K-MEANS clustering method was utilized, while applying Pearson or Spearman correlation analysis to examine correlations. A *P*-value of 0.05 or less was considered statistically significant.

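### About half of the nights in the first post-treatment PSQI window precede treatment, so the Week 3 sleep comparison is biased toward no difference

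*Protocol article*

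**What the plan says.** Four statements in the protocol article bear on this point.

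- **Recall period (section 2.8.2):** "The PSQI scale is used to assess the sleep quality of the patient in the past month". In the next item of the same section, "The N-QOL scale is used to assess the quality of life of the test subject in the past 2 weeks".
- **Course length (section 2.5.2):** "One treatment cycle consists of 5 days of treatment followed by 2 days of rest, with 2 consecutive treatment cycles being administered". Table 1 agrees: "Treatment phase Week 1-2".
- **First post-treatment reading (section 2.7):** "Upon completion of the treatment regimen, the PSQI, N-QOL scale scores, and traditional Chinese medicine syndrome score will be reassessed". Section 2.12 sets data collection at "the day after the end of treatment and 2 months after the end of treatment", and Table 1 places the first of these visits in Week 3.
- **Second post-treatment reading (section 2.7):** "with a further assessment conducted 2 months after the conclusion of therapy", which is Week 10 in Table 1.

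Sleep quality is the first secondary outcome listed in section 2.8.2 and is named in the secondary hypothesis (section 2.3). The article does not mention the overlap between recall windows and gives no adapted PSQI instruction. Section 2.12 handles missing data in the intention-to-treat analysis by last observation carried forward (LOCF), with multiple imputation as a possible alternative.

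**The concern.** A one-month questionnaire given right after a two-week course asks the patient to summarise a period of which only about half follows the start of treatment. The rest was already covered by the baseline PSQI. The three design elements (recall period, course length, assessment day) are each stated, and they do not fit together. The N-QOL, with its two-week recall, does fit the course.

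Two readings of the results are at stake. First, a real effect on sleep would be understated at the end of treatment, and a null Week 3 result could be taken as evidence against the secondary hypothesis. Second, the Discussion stresses durability two months after treatment. A comparison of Week 3 with Week 10 would set a mixed window against one with no pre-treatment nights, so its shape over time cannot be read at face value.

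**Working it through.** The article gives no PSQI effect size, standard deviation or power figure, so there is no PSQI calculation to reproduce. The preliminary sample size in section 2.9 reproduces as 1.96² × 0.5 × 0.5 / 0.10² = 96.04, but no PSQI quantity enters it.

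**Inputs**
- Course: 2 × (5 + 2) = 14 days (section 2.5.2; Weeks 1-2 in Table 1).
- Reading: the day after, i.e. day 15 (section 2.12), which falls in Week 3. Nights since the first session: T = 14.
- Recall window: one month. Its length in nights is not given, so I take W = 28, 30 and 31 as an assumed range.

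**Share of the window before the first session** = (W − T) / W

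| W | Pre-treatment nights | Pre-treatment share | Share since first session |
|---|---|---|---|
| 28 | 14 | 14/28 = 50.0% | 14/28 = 50.0% |
| 30 | 16 | 16/30 = 53.3% | 14/30 = 46.7% |
| 31 | 17 | 17/31 = 54.8% | 14/31 = 45.2% |

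If baseline is taken on the day of the first session, all 14-17 pre-treatment nights also lie in the baseline window.

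**Dilution at Week 3.** Assume that the effect is present in full from the first night and that the score averages evenly over nights. With an on-treatment group difference D, the difference seen at Week 3 is D × T/W, i.e. 0.45 D to 0.50 D.

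**Week 10.** Eight weeks after Week 2 is about 56 days. A window of 28-31 nights then opens about 56 − 31 = 25 to 56 − 28 = 28 days after treatment ends. It holds no pre-treatment nights, and no treatment nights either.

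**Time course, under the same assumptions**
- Constant true difference D: Week 3 shows 0.45-0.50 D and Week 10 shows D. The difference appears to grow by a factor of 28/14 = 2.0 to 31/14 = 2.2 although nothing changed.
- True difference halved by Week 10: Week 3 shows 0.45-0.50 D and Week 10 shows 0.50 D. A fading effect looks maintained.

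**LOCF.** Section 2.9 allows up to 15% dropout. As an upper bound, suppose all of it occurs after Week 3, evenly in both arms. With a constant D, the Week 10 difference becomes 0.85 D + 0.15 × (0.452 to 0.50) D = 0.918 D to 0.925 D. The carried-forward values bring some dilution back at Week 10, but much less than at Week 3.

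**The case against.** The strongest reply is that this touches one visit of one secondary outcome, in the conservative direction. That stands. The overlap is the same in both arms and cannot produce a false benefit. The primary outcome is a 72-hour diary. End-of-treatment sleep is not left to the PSQI alone either: section 2.8.2 also lists sleep duration, and the N-QOL has seven energy/sleep questions with a two-week recall.

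It can also be said that Week 10 is no substitute for an end-of-treatment reading, because it answers a question about persistence. That stands too, and is a cost of the fix.

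A reader might infer more than the document supports:
- **That more than half of the score describes untreated nights.** The arithmetic gives a share of nights. The PSQI is the sum of seven parts rated 0-3, and patients may weight recent nights more, so the score need not dilute in proportion. With a 28-night month the share is exactly half.
- **That the pre-treatment share reaches 57-61%.** This counts only the 12 days up to the last session (16/28 to 19/31). A reading on day 13 would fall in Week 2, whereas a cycle includes its rest days and Table 1 puts the visit in Week 3. Conversely, a reading at the end of Week 3 would lower the share to 25-32% (7/28 to 10/31), but section 2.12 fixes the day after treatment ends.
- **That the sample size for sleep is short by a known factor.** The article makes no power claim for the PSQI and gives nothing from which to compute one.
- **That any increase from Week 3 to Week 10 is only the window clearing.** Real growth, masked fading or drift are equally possible, and section 2.12 names no Week 3 versus Week 10 test. Clearing is one contributor.

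**Conclusion.** The mismatch is real and follows from the article's own recall period, course length and assessment day. At the first post-treatment reading, 50-55% of the nights in the PSQI window precede the first session, for a month of 28-31 nights. The bias is toward no difference. The estimate that 45-50% of the on-treatment difference would be seen rests on even recall and an immediate effect, neither of which the document establishes. A slower onset would lower that figure, and heavier weighting of recent nights would raise it.

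The Week 10 PSQI is free of the overlap where it is observed, but not where a Week 3 value is carried forward. The point affects the interpretation of a hypothesised secondary outcome, not the trial's main conclusion. It is worth correcting because the remedy is cheap.

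**What to change.** 1. State in section 2.12 that Week 10 is the inferential time point for the PSQI.
2. Report Week 3 PSQI descriptively, saying that about half of its recall window precedes treatment and overlaps baseline, and do not read the change from Week 3 to Week 10 as growth or maintenance.
3. Do not carry Week 3 PSQI forward into Week 10. Use multiple imputation, which section 2.12 already allows.
4. For sleep at the end of treatment, rely on the N-QOL energy/sleep items, whose two-week window matches the course.

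A declared two-week PSQI recall at every visit in both arms is an option only if it can be applied from baseline. Section 2.2 schedules conduct from January 2024, so this may no longer be open.

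Items 1-4 need a few sentences and no new data. The price is that Week 10 measures persistence and may miss a short-lived benefit. A changed recall period would depart from the PSQI window that the plan states.

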#### 2.8.3 Safety

All adverse events and vital signs will be observed and reported according to the standard operating protocol (SOP), especially the integrity of the skin at the moxibustion site.

### 2.9 Sample size

Based on relevant research (significance level, take α = 0.05, β = 0.10, test power 1-β = 0.90; two-sided test, confidence level 95%, *Z* = 1.96, *E* = 10%, *P* = 0.5), the estimated sample size is 96 cases preliminary. If the dropout rate is considered to be at most 15%, the total number of cases in the two groups should be at least 110. Therefore, 55 participants were recruited in each group.

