### 2.8 Outcome measures

#### 2.8.1 Primary outcomes

The frequency of nocturia: 72-hour urination diary.

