
This study aims to have a sample size of 110 patients, which will be one of the largest randomized controlled trials in this field. The target is to demonstrate the effect of HSM on nocturia in the elderly, clarify the amount of moxibustion, the distribution pattern of thermosensitive acupoints, the frequency of thermosensitive acupoints and the moxibustion sensation for the treatment of nocturia, and further clarify the regulatory effect of HSM on AVP and ANP, to provide experimental data for clarifying the therapeutic mechanism of HSM on nocturia in the elderly and direction for future basic research. Compared to previous studies (29, 30), our study boasts a shorter treatment duration, which is more readily acceptable to patients. Furthermore, our protocol places emphasis on the long-term maintenance effects of HSM, with reassessments of outcome measures conducted 2 months after treatment. Additionally, we aim to investigate the underlying regulatory mechanisms by analyzing and comparing changes in AVP and ANP levels before and after treatment. To ensure the integrity and scientific validity of the method, every step of the implementation of this clinical study will be strictly carried out, monitored and supervised.

Here are the limitations of our study: Firstly, the inclusion of only a limited number of patients as samples may restrict the representativeness and generalizability of our findings. Secondly, being a single-center study, our research may be influenced by the specific practices, patient demographics, or resource constraints of the institution, thereby limiting the broad applicability of our results. Lastly, with a follow-up period of just 2 months, our study may not adequately capture all significant clinical changes or adverse events associated with a chronic condition such as nocturia.

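### The 96 in the sample size section is a one-sample precision figure for a single proportion, so the stated 90% power is unsupported for the two-arm comparison of nocturia frequency

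*Protocol article*

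**What the plan says.** Section 2.9 lists its error rates as "significance level, take α = 0.05, β = 0.10, test power 1-β = 0.90". It adds a two-sided test, a 95% confidence level, Z = 1.96, E = 10% and P = 0.5. E and P are not defined. It continues: "the estimated sample size is 96 cases preliminary. If the dropout rate is considered to be at most 15%, the total number of cases". It sets that total at a minimum of 110, which gives 55 per group. The Discussion repeats the total: "This study aims to have a sample size of 110 patients".

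The primary outcome in section 2.8.1 is "The frequency of nocturia: 72-hour urination diary", and the abstract describes it as the reduction in that frequency. Section 2.12 compares continuous outcomes between groups by Student's t-test, or by the Mann-Whitney U test if the data are not normal. It analyses both an intention-to-treat and a per-protocol population, and in the former it fills missing values by last observation carried forward. Section 2.9 states no between-arm difference in nocturia frequency, no SD and no pair of response rates.

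**The concern.** The paragraph reads as a power calculation, but its numerical inputs are those of a survey precision calculation. For a comparison of mean night-time voids between two arms, one expects a target difference, an SD and a normal quantile for power (1.28 for 90%). None of these appears. There is one proportion and one quantile, and that quantile belongs to the confidence level.

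The stake is what a reader may conclude from the result. Power is always power for some effect. A 90% figure with no effect attached does not tell a reader which difference the trial could have missed, and so does not help in reading a non-significant result. The step from 96 to 110 also looked short of what 15% dropout requires.

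**Working it through.** **Inputs from section 2.9.** Alpha 0.05 two-sided, beta 0.10, Z = 1.96, E = 0.10, P = 0.5, N before dropout 96, dropout at most 15%, total 110, 55 per arm.

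**Step 1: reproduce 96.** The precision formula for one proportion in one sample is n = Z² P(1 − P) / E².

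1.96² × 0.5 × 0.5 / 0.10² = 3.8416 × 0.25 / 0.01 = 96.04.

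This matches the stated 96. Beta does not enter the formula, and neither does the number of arms, a difference between arms or an SD. The same 96 would follow if power were stated as 80% or 99%.

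**Step 2: reproduce 110.**

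- 96 × 1.15 = 110.4, stated as 110. This adds 15% to the starting figure.
- To have 96 left after 15% loss, the divisor is 1 − 0.15: 96 / 0.85 = 112.9, so 113, or 114 for equal arms (57 each).
- Check: 110 × 0.85 = 93.5, which is below 96.

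The gap is 3 patients (4 with equal arms).

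**Step 3: what 110 delivers for the planned test.** The plan gives no difference or SD, so the result can only be expressed in SD units. For a two-sample t-test, two-sided 5%, the normal approximation to the detectable standardised difference is d = (z for alpha + z for power) × √(2 / n per arm).

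- 55 per arm, 90% power: (1.960 + 1.282) × √(2/55) = 0.618.
- 46.75 per arm (55 × 0.85), 90% power: 3.242 × √(2/46.75) = 0.670.

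The exact calculation with the noncentral t distribution gives slightly larger values:

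| Analysed per arm | d for 90% power | d for 80% power | Power at d = 0.5 | Power at d = 0.4 |
|---|---|---|---|---|
| 55 (no loss) | 0.624 | 0.539 | 74% | 55% |
| 46.75 (15% loss) | 0.678 | 0.586 | 67% | 48% |

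**Step 4: illustration in voids per night.** The SD is an assumption, because the article gives none. With an SD of 1.0, the 90% range is 0.62 to 0.68 voids per night. With an SD of 1.5 it is 0.624 × 1.5 = 0.94 to 0.678 × 1.5 = 1.02.

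**The case against.** The total of 110 may be perfectly adequate. If the true standardised difference is about 0.62 or more with everyone analysed, the trial has at least 90% power. A reader might infer from the faulty derivation that the trial is underpowered. The article does not support that: without a difference or SD, its actual power is unknown in either direction.

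A reader might also take E = 10% as a between-arm difference in proportions and judge power on that basis. Section 2.9 does not define E that way, the figure of 96 is not reproduced that way, and the primary outcome is a frequency, not a proportion. That reading says nothing about this trial.

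On dropout, 15% is stated as an upper bound, the shortfall is three or four patients, and the intention-to-treat analysis with carried-forward values keeps participants who leave. This stands, and it makes the dropout arithmetic secondary. It is also why the detectable difference should be given as a range: 0.62 SD assumes that all 55 per arm contribute fully, 0.68 SD assumes that 15% contribute nothing, and carried-forward values carry less than full information.

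Finally, section 2.9 refers to relevant research, and a journal article condenses its source. That would explain a missing citation or a missing SD. It does not explain 96, because the printed inputs give that number by the one-sample formula and leave beta unused.

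**Conclusion.** The point holds, and it must be corrected. The 90% power in section 2.9 is not a property of the calculation shown there, and it is unsupported for the two-arm comparison of nocturia frequency. The reproduction of 96 needs no assumption beyond the printed inputs. It is a finding about the justification of the sample size, and it leaves open whether 110 is too few.

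What 110 supports is 90% power at about 0.62 to 0.68 SD and 80% power at about 0.54 to 0.59 SD. These ranges assume a two-sided 5% t-test, equal arms, approximate normality, and loss between 0% and 15%. They would need re-checking if the Mann-Whitney test is used.

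The dropout inflation is wrong by three patients (four with equal arms) and would not justify a finding alone.

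**What to change.** In section 2.9, delete the derivation from Z, E and P and the unconditional 90% power claim. Keep N = 110 and replace the paragraph with text along these lines:

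> The planned total is 110 participants, 55 per arm. For a two-sided 5% two-sample t-test of nocturia frequency, this gives 90% power to detect a between-arm difference of about 0.62 SD if all participants are analysed, and about 0.68 SD if 15% are lost (80% power: about 0.54 and 0.59 SD). With an SD of [value, source] voids per night, these correspond to differences of [values] voids per night.

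The authors must supply the SD and its source, and should say whether a difference of that size is clinically plausible. Once the formula is removed, 96 is no longer a requirement and should not be kept as a target for evaluable participants. Any dropout allowance should be computed as N / (1 − dropout).

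The cost is one rewritten paragraph, with no extra patients and no change to procedures or to the analysis. The resulting statement is less favourable than a bare 90%, but readers can use it.
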